#### Participant timeline

Figure 1 presents the schedule for enrollment, evaluation of research outcome measures, and others for participants.

**Fig. 1 Fig1:**
[figure not shown]
Schedule of the major study events

We will perform upper gastrointestinal endoscopic sedation on the first day, and the baseline data of participants will be collected and randomized before conducting the procedure. Participants’ vital signs will be monitored. Adverse events will be assessed, and drug combination will be recorded during the whole procedure.

#### Sample size

In this study, the noninferiority test will be performed between the experimental and control groups (i.e., experimental group 1 vs. control group; experimental group 2 vs. control group). Assume that the success rate of sedation in the propofol group is 100% and that in each remimazolam tosylate group is 95%. Considering the first type of error, *α* = 0.0125 (single-sided), 90% power, and 10% dropout rate, 600 participants are required for each group, with a total of 1800 for the three groups.

#### Allocation masking

This study follows a single-blinded method. All participants are blinded to the assignment of the trial (the injection site will be shielded) and will be randomly assigned to any of the three groups.

#### Unblinding procedures

Because the trial is single blind, participants interested in knowing their group can be informed by the investigator after analyzing the results.

#### Plans for communicating important protocol modifications to relevant parties

All changes in the study protocol will be reviewed by the ethical committee, which will be reported to the sponsor, participating care providers, and investigators.

#### Composition of the data-monitoring committee and its role and reporting structure

We have not considered the need for a data-monitoring committee.

#### Interim analyses

No formal interim analysis of the primary and secondary outcomes is planned.

#### Frequency and plans for auditing trial conduct

We have no plans for auditing trial conduct in this investigator-initiated pragmatic trial.

#### Data management

All participants’ data collected during this clinical study will be entered and/or filed in the respective participants’ case report forms (CRFs). Data on each patient’s study participation must be documented appropriately in the CRF with study number, participant number, date of collection of participant information, and informed consent. The source data should be filed based on the GCP guidelines. The data manager will be responsible for data processing based on the sponsor’s standard operating procedures and will conduct regular monitoring to ensure that dates are adequate, accurate, and complete. Database lock will occur only after completing the quality assurance procedures.

#### Statistical analysis

Data selection for statistical analysisFull analysis set (FAS): Based on the principle of intention-to-treat analysis, the full analysis set will include all participants who enroll in the study and receive at least one dose of the treatment.Per-protocol set (PPS): The PPS population will include all FAS participants without major protocol deviations that influence the evaluation of the primary outcomes. Efficacy analysis will be performed on the FAS and PPS.Safety analysis set (SAS): The safety population consists of all participants who receive at least one dose of the treatment. Analyses of the safety data in this study will be based on the safety population.

##### Statistical analysis plan

All statistical analyses in this experiment will be programmed and calculated using the SAS analytics software version 9.4. In this study, the noninferiority one-sided test used for the main efficacy outcome is that a *P*-value of ≤0.0125 will be considered statistically significant. All other tests will be two-sided tests, with a *P*-value of ≤0.05 considered statistically significant, and the confidence interval will be set at 95%.

Measurement of basic data in different treatment groups will be statistically expressed as mean ± standard deviation or median (interquartile range [IQR]).

The *χ*^2^ test will be used for the success rate of sedation, incidence of injection pain, hypoxia, and adverse events. The analysis of variance will be used to induce time of sedation, full alertness, and discharge. The rank sum test will be used for calculating the satisfaction of endoscopists and participants.

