**Discussion:**

This study will determine the optimal dosage of remimazolam tosylate during upper gastrointestinal endoscopy and will describe its efficacy and safety. These findings may contribute to a more comfortable and safer experience for patients compared with that when the conventional sedative propofol is used.

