#### Allocation

Participants will be randomly assigned to one of the following three groups: experimental group 1 (remimazolam tosylate 0.15 mg/kg), experimental group 2 (remimazolam tosylate 0.2 mg/kg), or control group (propofol 1.5 mg/kg). A central randomization system will be used to randomize the participants. The system is stratified by each center, and the block length is six. Using the allocation sequence of the central randomization system, participants will be randomly assigned in a 1:1:1 ratio to experimental group 1, experimental group 2, or control group. Eligible participants will receive a unique random number upon enrollment. If multiple participants are scheduled on the same day, randomization will be performed based on the time of the participants’ arrival rather than the sequence of screening.

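### Testing both doses at a fixed one-sided 0.0125 is valid, but Holm's step-down rule would be more efficient at the same implied familywise error

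*Protocol article*

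**What the plan says.** The Sample size section of the protocol article names two comparisons: "experimental group 1 vs. control group; experimental group 2 vs. control group". It assumes 100% success on propofol and 95% on each remimazolam dose, and sets the size from "0.0125 (single-sided), 90% power, and 10% dropout rate, 600 participants are required for each group". The Allocation section gives equal allocation to the three arms.

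The Statistical analysis plan section carries the same level into the decision rule. For the one-sided noninferiority test on the main efficacy outcome, a P-"value of ≤0.0125 will be considered statistically significant". That threshold does not depend on how the other dose fares. No step-down, hierarchical or gatekeeping rule appears in the article, and no multiplicity method is named. No noninferiority margin is given either. The abstract states the wider aim: "This study will determine the optimal dosage of remimazolam tosylate".

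**The concern.** The evident origin of 0.0125 is one-sided 0.025 divided equally between two tests. Applied as a fixed threshold to both, it is the Bonferroni rule, and it stays at 0.0125 for the second dose even after the first has passed. Holm's procedure starts at the same 0.0125 and then allows 0.025 for the remaining dose.

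At stake is the second verdict. Suppose one dose passes and the other has a one-sided p-value between 0.0125 and 0.025. The fixed rule withholds the noninferiority claim for the second dose, although the familywise budget would allow it. A trial that studies two doses against one comparator has reason to want a confirmatory answer on each, and the stated 90% power is read here as applying to each comparison separately.

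**Working it through.** **Inputs.** From the Sample size section: one-sided 0.0125, 90% power (taken as per comparison), 95% against 100% success, 10% dropout, 600 per arm. Evaluable per arm: 600 × 0.9 = 540. Assumed: familywise level 2 × 0.0125 = 0.025, and the margin M, which the article does not state.

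**The plan's own figures.** The level reproduces: 0.025 / 2 = 0.0125. The 600 cannot be checked without M, but M can be back-solved. With unpooled variance, n = (2.241 + 1.282)² × (0.95 × 0.05 + 0) / (M − 0.05)². At M = 0.083 this is 12.41 × 0.0475 / 0.001089, about 542 evaluable, and 542 / 0.9 gives 603. So 600 fits a margin near 8.3 points under this formula. A Farrington–Manning calculation gives 589 at 9 points, so the implied margin also depends on the method.

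**Correlation.** The two comparisons share the control arm. At 100% control success the assumed control variance is zero, so the statistics are uncorrelated under the plan's own assumption. Correlation 0.5 is shown as a sensitivity case.

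**If 90% per dose holds.** The shift is 2.241 + 1.282 = 3.523. Let a be power at 0.0125 and b power at 0.025:
- a = 0.900; b = Φ(3.523 − 1.960) = 0.941.
- Both doses, fixed rule: a² = 0.810.
- Both doses, Holm: b² − (b − a)² = 0.8854 − 0.0017 = 0.884.
- One given dose, Holm: a + (b − a) × a = 0.900 + 0.041 × 0.900 = 0.937.
- At least one dose, either rule: 1 − (1 − a)² = 0.990.

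At correlation 0.5, both doses go from 83.2% to 89.4% and per-dose power from 90.0% to 93.1%; at least one stays at 96.8%.

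**Familywise error under Holm.** If both doses are inferior, an error requires the smaller p-value to be ≤ 0.0125. The probability is at most 2 × 0.0125 = 0.025, and 1 − 0.9875² = 0.0248 if independent. If only one is inferior, it can be claimed only with p ≤ 0.025, so the error is again at most 0.025. Neither bound depends on the correlation.

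**Dependence on the margin.** With 540 evaluable per arm, SE = √(0.0475 / 540) = 0.00938 and the shift is (M − 0.05) / SE. At correlation 0:

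| Assumed margin (points) | Per dose, fixed | Both, fixed | Both, Holm | Gain (points) |
|---|---|---|---|---|
| 7 | 45.7% | 20.9% | 31.1% | 10.2 |
| 8 | 83.1% | 69.0% | 79.2% | 10.2 |
| 8.3 (gives 90%) | 90.0% | 81.0% | 88.4% | 7.4 |
| 9 | 97.9% | 95.7% | 97.9% | about 2 |
| 10 | 99.9% | 99.8% | 99.9% | about 0.1 |

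**The case against.** The strongest reply is that nothing is wrong. The trial is sized at 0.0125 and tested at 0.0125, and the two sections agree. Choosing one valid multiplicity method over another can be called a preference. This stands in part: the fixed rule is not an error. But the article does commit to a specific rule, and that rule is uniformly no better than an alternative that uses the same first threshold and the same sample.

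The second reply is that the gain is uncertain and narrow. This stands. It depends on a margin the article does not give, it falls to almost nothing at 10 points, and the chance of at least one success does not move. Only its direction is certain.

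The third reply is that the change has a cost. This also stands. Fixed 0.0125 pairs each dose with the same two-sided 97.5% interval, whereas Holm has no simple matching simultaneous intervals. Only participants are masked (Allocation masking), so relaxing a primary threshold after the start could look data-driven, and protocol changes go to the ethics committee (Plans for communicating important protocol modifications).

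Two stronger readings are tempting. A reader might infer that the power statement is false because the chance of showing both doses is only 81%. The article does not support that: it sets two separate comparisons and nowhere requires both to succeed. A reader might also infer that verdicts on both doses would settle the optimal dose. They would not, because neither comparison sets one dose against the other.

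**Conclusion.** The point holds as an optional gain in efficiency. On the plan's own assumptions, and if 90% per-dose power is real, Holm adds about 7 points to the chance of showing both doses noninferior (about 6 at correlation 0.5) and 3 to 4 points per dose, with no extra participants and the familywise error still at most 0.025.

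Three assumptions carry this: the familywise level is 2 × 0.0125, the 90% applies to each comparison, and the unstated margin is near 8.3 points under the unpooled formula. Across margins of 7 to 10 points the both-dose gain runs from about 10 points to about 0.1. It is never negative. A separate statistical analysis plan, not at hand, might already contain a step-down rule; the article gives no sign of one.

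**What to change.** By protocol amendment, before any comparative data are examined, state that the two noninferiority tests follow Holm's procedure at one-sided familywise 0.025: the smaller p-value is compared with 0.0125 and, only if it is significant, the larger with 0.025. Keep 600 per arm and 0.0125 as the planning level. If comparative data have already been seen, leave the fixed rule in place.

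Report two-sided 97.5% intervals for both doses beside the Holm decisions. Say in advance that a dose passing only at the second step can have a 97.5% interval that crosses the margin.

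The cost is the amendment with its ethics review and notification, plus the looser link between intervals and decisions. No participants are added.

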##### Additional analyses

Subgroup analysis: Subgroup analysis via an interaction by gender, age (18–24, 25–44, and 45–60 years), and BMI (<23 and ≥23 kg/m^2^) will be used to analyze the primary and secondary outcomes among subgroups.Safety analysis: General safety evaluations will be based on the incidence and type of adverse events. Safety variables will be tabulated and presented for all participants in the safety set. Adverse events will be coded using the World SIVA adverse sedation event reporting tool. The number (%) of participants with any adverse events will be summarized.

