## Discussion

Our previous study demonstrated that most patients (85.4%) felt uncomfortable during unsedated gastroscopy and 2.1% of the patients reported extreme discomfort. Vomiting/retching was the most common adverse event reported during unsedated gastroscopy. A larger number of gastroscope-intubation attempts and a longer procedure time were needed for unsedated gastroscopy. Therefore, sedative gastroscopy is essential for patients [20]. However, the sedation rate for gastrointestinal endoscopy is much lower in China than in the USA and Europe [21].

Significant developments in endoscopic sedatives have been made in the past decade with participant safety and comfort being the primary focus. However, sedation increases the costs and poses a risk for complications [22].

In the past, propofol and midazolam were the main drugs used for gastrointestinal endoscopic sedation [1]. Propofol is the preferred medication, especially by anesthesiologists. However, propofol use is usually associated with hemodynamic suppression [23]. It is a very negative inotropic drug wherein any decrease in the cardiac output cannot be compensated by an increase in the heart rate. Furthermore, propofol inhibits the sympathetic tone, indicating that cardiac output often drops significantly after a bolus dose. This is most pronounced in patients with impaired cardiac function, especially the elderly and neonates. Propofol induces dose-dependent respiratory depression, whose incidence and duration depend on age, dose, rate of injection, and co-administration of other sedatives/analgesics [24].

Midazolam is the most commonly used sedative drug because of the legal restriction of propofol. Midazolam has a slower onset of action and a relatively longer half-life time (1 h). It is metabolized into active metabolites and interacts with all drugs metabolized through the cytochrome P450 pathway [25]. Furthermore, the creation of active metabolites may lead to a longer and less predictable recovery from sedation [8]. Considering the increasing demand for gastrointestinal endoscopy and disadvantages of existing anesthetics, the development of more effective agents with a more tolerable profile is required urgently.

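### Induction, full-alertness and discharge times are compared by analysis of variance with no covariate named, which costs a modest amount of precision on secondary outcomes

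*Protocol article*

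**What the plan says.** The Statistical analysis plan section of the protocol article assigns one method to the three durations: "The analysis of variance will be used to induce time of sedation, full alertness, and discharge". No covariate, stratification factor or transformation is attached to it. The significance rule for these outcomes is: "All other tests will be two-sided tests, with a *P*-value of ≤0.05 considered statistically significant". In the same section satisfaction gets a rank sum test, and baseline data may be summarised by mean and SD or by median and IQR.

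The variables that could serve as covariates are already in the design:

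- **Center.** The Allocation section stratifies randomization by center, with blocks of six.
- **Age, sex and BMI.** The Additional analyses section plans "Subgroup analysis via an interaction by gender, age (18–24, 25–44, and 45–60 years), and BMI", and says this "will be used to analyze the primary and secondary outcomes among subgroups". The three times are secondary outcomes, so they are covered, but only through interactions and with age and BMI in categories.
- **Timing.** According to the text with Fig. 1, "the baseline data of participants will be collected and randomized before conducting the procedure", so these variables are recorded before treatment.

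**The concern.** In a randomized comparison, variation in the outcome that pre-treatment variables explain can be removed from the error term at no cost in participants. The stated method leaves it there. Center has the clearest design reason for inclusion. Stratified blocks balance the arms within center, but an analysis without center still counts between-center variation as noise, so the reported standard error is larger than the design warrants.

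A second point concerns scale. Induction time runs from the first dose to the first MOAA/S score of 2 or less (Outcome measures). Under Procedure of the trial, a participant still above 2 after two minutes receives top-ups at least one minute apart. Most induction times should therefore be short, with a tail to the right. If the analysis is run on untransformed times, a few long values inflate the pooled variance.

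At stake is the width of the intervals for onset and recovery. The Discussion links these to its case for studying the initial dose, where it doubts that the earlier fixed 5.0 mg dose sedates fast enough. The primary noninferiority test is not affected.

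**Working it through.** **The plan's own figure.** The document states no mean, SD, skewness or power for the three times, so there is nothing to reproduce for them. The 600 per group in Sample size belongs to the primary outcome and is taken here as given. With 10% dropout, 600 × 0.9 = 540 are evaluable per arm.

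**Inputs.** From the document: 600 per arm, 10% dropout, two-sided 0.05. Assumed, and shown as ranges: R², the share of outcome variance that the covariates explain jointly, and the SD of log time (s).

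**1. What the unadjusted comparison can already detect.** The smallest difference detectable with 90% power, in SD units, is (1.960 + 1.282) × √(2/540) = 0.197. At 80% power it is 0.170.

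**2. Gain from covariates.** The standard error is multiplied by √(1 − R²). The equivalent extra sample is 600/(1 − R²) − 600.

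| Assumed R² | Cut in SE | Detectable difference, 90% power, 540 per arm | Equivalent extra participants per arm of 600 |
|---|---|---|---|
| 0.01 | 0.5% | 0.196 SD | 6 |
| 0.05 | 2.5% | 0.192 SD | 32 |
| 0.10 | 5.1% | 0.187 SD | 67 |

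For example, 600/0.95 = 631.6, a gain of 32, and 600/0.90 = 666.7, a gain of 67.

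**3. Effect of scale, if times were lognormal.** A small shift δ in log time moves the raw mean by about mean × δ. The raw SD is mean × √(exp(s²) − 1) and the log SD is s. The efficiency of the raw scale relative to the log scale is therefore s²/(exp(s²) − 1).

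| Assumed s | Raw-scale efficiency | Equivalent loss per arm of 600 |
|---|---|---|
| 0.4 | 0.16/0.1735 = 0.922 | 47 |
| 0.5 | 0.25/0.2840 = 0.880 | 72 |
| 0.6 | 0.36/0.4333 = 0.831 | 102 |
| 0.8 | 0.64/0.8965 = 0.714 | 172 |

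**4. Validity check by simulation.** Three arms of 540 were simulated with lognormal times of equal log-SD, 3,000 runs per setting. For power, both experimental arms were shifted by 3 × s × √(2/540) on the log scale.

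| s | Type I error, raw | Power, raw | Power, log |
|---|---|---|---|
| 0.3 | 0.053 | 0.85 | 0.87 |
| 0.5 | 0.052 | 0.83 | 0.88 |
| 0.8 | 0.041 | 0.74 | 0.88 |
| 1.0 | 0.052 | 0.65 | 0.87 |

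The raw analysis keeps its nominal 5% level throughout. What it loses is power: 2 to 5 points at s of 0.3 to 0.5, and much more only under strong skew.

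**The case against.** The strongest objection is that this is detail a condensed article leaves to the analysis plan. Analysis of variance is valid at this sample size, and preferring a covariate-adjusted model is a matter of taste on unpowered secondary outcomes. Part of this stands. A separate plan may name covariates or a transformation, and the simulation supports validity. But the article does name a method for these outcomes, and a more precise one is available from data it already holds.

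The gain may also be small. Eligibility narrows age (upper limit 60), BMI (18 to 28 kg/m²) and ASA class (I–II), and dosing is by weight. Both may limit what age and BMI explain. That stands, and is why the claim is kept modest.

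Several stronger readings are tempting, but the documents do not support them:

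- **That the plan ignores age, sex and BMI.** Additional analyses uses all three for these outcomes. What is absent is adjustment of the main comparison.
- **That the plan fixes the untransformed scale.** This is the plain reading of an unqualified analysis of variance, but it is inferred from silence.
- **That all three times are skewed by top-ups.** The alertness and discharge clocks start when drug administration ends, after any induction delay. The top-up argument covers induction time only, and a top-up tail need not be lognormal.
- **That the article itself says age drives these times.** The Discussion phrase "whose incidence and duration depend on age, dose, rate of injection, and co-administration of other sedatives/analgesics" concerns propofol's respiratory depression.
- **That these times carry the trial's claim.** Aims and objectives rests on completion, vital signs and satisfaction.

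**Conclusion.** The point holds as a modest loss of precision on three secondary outcomes. With center, age, sex and BMI left out of the main comparison, the standard error is about 2.5% to 5% larger than it need be if they jointly explain 5% to 10% of the variance. Both ends of that range are assumptions; at 1% the gain is negligible. About 540 evaluable per arm already detect roughly 0.20 SD with 90% power, so few conclusions are likely to turn on this.

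The scale could matter more, but its size cannot be fixed from the document. The raw scale would lose about 8% to 29% of efficiency if times were lognormal with log-SD 0.4 to 0.8, and only for induction time does the document give a reason to expect skew.

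A reader might infer that skew makes the test invalid. The simulation does not bear that out when spread on the log scale is equal across arms. Markedly unequal spread would be a different matter, and the document gives no information on it.

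**What to change.** Before database lock, replace the sentence on the three times with a prespecified linear model for each one, containing arm, center, continuous age, continuous BMI and sex. Report each remimazolam dose against propofol as a difference in time with its 95% interval. Keep the unadjusted analysis of variance as a sensitivity analysis. The categorical age and BMI bands can remain for the subgroup interactions.

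For induction time, add a supporting analysis of log time that gives the ratio of geometric means of each dose to propofol with its 95% interval, and show medians (IQR) alongside. It is best kept as support: its downside is that effects are expressed as ratios, whereas a difference in time units may be easier to use in practice.

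The cost is analysis wording and a little programming. No new data, visits or participants are needed, and the primary analysis and sample size do not change.
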